Regarding Aim 2, we will examine the effect of RT on 5-year mortality and its interaction with comorbidity burden in older women with low-risk breast cancer (n=634) using Kaplan-Meier survival analysis and a IPTW-adjusted Cox regression model. We hypothesize that receiving adjuvant RT will improve 5-year mortality, but the magnitude of improvement will differ by comorbidity burden class. We expect that women who have the lowest comorbidity burden and also receive RT will experience the greatest improvement in survival outcomes.

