**Figure 1 figure1:**
[figure not shown]
Overview of the proposed retrospective cohort study design. The study population will comprise older women with low-risk breast cancer who received breast-conserving surgery (BCS) as a primary treatment in 1998-2014 and took part in Medicare Health Outcomes Survey (MHOS). The women were first clustered according to their prediagnosis comorbidity burden using latent class analysis. Next, the propensity score-based probability of receiving adjuvant radiotherapy (RT) will be obtained, and inverse probability of treatment weights (IPTW) will be estimated and included in statistical models. To examine the effects of RT on 2 outcomes, health-related quality of life (HRQOL) trajectories over 10-year follow-up periods and 5-year survival outcomes, IPTW-adjusted multilevel growth mixture models and IPTW-adjusted Cox proportional hazards regression models will be used, respectively. The data are sourced from the SEER-MHOS Database. ER: estrogen receptor.

We will utilize the Surveillance, Epidemiology, and End-Results (SEER) database linked to the Medicare Health Outcomes Survey (MHOS) for this project. The SEER-MHOS database resulted from the collaborative efforts of the National Cancer Institute (NCI) and the Centers for Medicare & Medicaid Services. SEER collects data on cancer incidence, treatment, and survival, covering nearly 28% of the United States population. SEER includes high-quality, reliable patient characteristic data (eg, demographics, initial treatment and treatment sequence, tumor characteristics, vital status, and cause of death), while the MHOS data provide patient-reported HRQOL outcomes, comorbidity, functional status, and symptoms for a randomly selected sample of the Medicare Advantage Organization enrollees. MHOS is a longitudinal, 2-wave survey administered twice within a cohort at a 2-year interval. Participants who responded to the first baseline survey may have completed the second follow-up survey. In addition, some participants were sampled in more than 1 cohort, resulting in multiple surveys in different years, which allows the evaluation of HRQOL change over time. Therefore, SEER-MHOS is the best available data source for examining the long-term HRQOL trajectory after diagnosis of cancer in a diverse elderly population with varying degrees of comorbidity burden even though SEER-MHOS is limited in its geographical coverage of the United States.

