#### Measurements

The primary exposure variable will be adjuvant RT. We will consider BCS alone and BCS with adjuvant RT as the treatments. The SEER data provide information on radiation treatment and the sequence of surgery and radiation.

The outcomes of Aim 1 will be HRQOL scores measured over a 5-10 years of follow-up (ie, prediagnosis through post-treatment). MHOS measures HRQOL using the Medical Outcomes Study 36-item Short Form (SF-36) through the year 2005 and the Veterans RAND 12-item Health Survey (VR-12) from the year 2006 onwards. These 2 questionnaires have been validated in many languages and are widely used in HRQOL research, including that involving breast cancer patients [38]. The NCI developed algorithms to convert SF-36 scales to VR-12 scales; hence, the latter will be used across all cohorts in the current study. The VR-12 items correspond to 8 health domains, namely physical functioning, role limitations due to physical problems, role limitations due to emotional problems, bodily pain, social functioning, mental health, vitality, and perceptions of general health. These 12 items are then summarized into 2 summary scores: the physical component summary score and the mental component summary score. These 2 summary scores are standardized scores (mean 50, SD 10), which are normed based on the general US population. A total of 465 women who met the eligibility criteria for Aim 1 completed MHOS multiple times (an average of 3 times). We will sort the data according to the prediagnosis (T_0_) and postdiagnosis (T_1_…T_10_) timelines, specifying the time lapse from the cancer diagnosis. The prediagnosis HRQOL (T_0_, n=465) will be assessed using the survey conducted within 24 months prior to the diagnosis date recorded in SEER. The postdiagnosis HRQOL (T_1_…T_10_) will be assessed using the survey completed after the diagnosis of breast cancer. We collected 465 data points for the precancer diagnosis, 508 data points within 2 years postdiagnosis, 166 data points for 2-<5 years postdiagnosis, and 92 data points for ≥5 years postdiagnosis. The number of patients who completed MHOS in each time frame is presented in Table 1.

**Table 1 table1:** Number of patients who completed MHOS in each time frame (N=465).

Survey time to cancer diagnosis (months), t	Prediagnosis and postdiagnosis HRQOL timelines	n (%)
–24<t<0	T_0_	465 (100)
0≤*t*<12	T_1_	253 (54)
12≤*t*<24	T_2_	255 (55)
24≤*t*<36	T_3_	79 (17)
36≤*t*<48	T_4_	50 (11)
48≤*t*<60	T_5_	37 (8)

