Regarding the estimation of RT and comorbidity effects on HRQOL trajectory, we will use a multilevel growth mixture model with surveys clustered within the women to test whether a difference exists in the patterns of HRQOL trajectories with receipt of RT and comorbidity class after controlling for confounders. At level 1, we will first regress woman i’s HRQOL change, which describes how each woman’s HRQOL depends on time t. This procedure will provide the intercept and slope of the time predictor for each woman. At level 2, we will regress each woman’s intercept and slope on her RT treatment (yes/no) and comorbidity class, adjusted for confounders. This procedure will feature how individual HRQOL change trajectories vary across treatment groups (RT) and comorbidity burden classes (COM). Equation (1) presents a simplified model with no covariates, predicting HRQOL from years after diagnosis (TIME), radiation treatment (RT), and comorbidity class (COM). It will estimate the intercepts and slopes for the group of women.

HRQOL_ti_ = γ_00_ + γ_01_RT_it_ + γ_02_COM_i_ + γ_10_TIME_it_ + γ_11_RT_i_TIME_it_ + γ_12_COM_i_TIME_it_ + error **(1)**

where

γ_00_=Estimated average HRQOL in the year of diagnosis for women who did not receive RT

γ_01_=Value added to the average HRQOL if the women received RT

γ_02_=Value added to the average HRQOL due to the comorbidity class

γ_10_=Change in HRQOL for all women for each year from diagnosis

γ_11_=Additional change for each year if the women received RT

γ_12_=Additional change for each year due to the comorbidity class

A significant negative value on γ_11_ will indicate that women who receive RT experience steeper declines in HRQOL over time than those who did not receive RT, while a significant negative value on γ_12_ will indicate stronger HRQOL declines due to the comorbidity burden.

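### Aim 1 reads RT and comorbidity effects from 10-year HRQOL slopes, but surveys well past year 2 come only from surviving, re-sampled women, and no Aim 1 analysis examines this

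*Protocol article*

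**What the plan says.** The Methods Overview sets the Aim 1 outcome as HRQOL trajectories over 10 years after diagnosis. It describes the source: "MHOS is a longitudinal, 2-wave survey administered twice within a cohort at a 2-year interval". Longer follow-up arises because "some participants were sampled in more than 1 cohort, resulting in multiple surveys in different years". The prediagnosis score (T0) comes from a survey in the 24 months before diagnosis (Aim 1, Measurements), and entry requires a survey both before and after diagnosis (Aim 1, Study Design and Study Population).

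The Aim 1 Measurements section reports 465 prediagnosis surveys, "508 data points within 2 years postdiagnosis", then "166 data points for 2-<5 years postdiagnosis, and 92 data points for ≥5 years postdiagnosis".

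The Aim 1 Statistical Analysis Plan regresses each woman's intercept and slope on RT and comorbidity class and fixes a reading: "A significant negative value on γ_11_ will indicate that women who receive RT experience steeper declines in HRQOL over time". It treats differing survey times as something growth mixture modelling accommodates, and its sensitivity item is subgroups by age and stage. The Aim 2 Statistical Analysis Plan, by contrast, includes a sensitivity analysis for informative censoring. The Limitations section does not mention death, disenrollment or non-response as a problem for the HRQOL analysis.

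**The concern.** A slope over 10 years is described for the whole cohort, but its later part is seen in few women, all of whom had to survive, stay enrolled, be sampled again and reply. If women whose HRQOL falls fastest are less likely to reach those surveys, for reasons that RT, comorbidity class and their recorded scores do not capture, the fitted average decline is too shallow and the comorbidity slope is pulled towards zero.

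RT could be affected in the other direction. The Introduction states: "We hypothesize that receiving adjuvant RT will improve 5-year mortality, but the magnitude of improvement will differ by comorbidity burden class". If RT does prolong life, frailer women stay measurable longer in the RT group than in the group with surgery alone. RT could then appear to go with a steeper decline without any effect on HRQOL, and the fixed reading of γ11 makes no allowance for that. The treatment weights are built from baseline characteristics, so they do not adjust for who is still surveyed later.

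**Working it through.** **1. The plan's counts reproduce.** From Table 1: 253 + 255 = 508; 79 + 50 + 37 = 166; 29 + 21 + 17 + 8 + 17 = 92. The total is 465 + 508 + 166 + 92 = 1,231 surveys, and 1,231/465 = 2.65 per woman. Surveys at ≥5 years: 92/1,231 = 7.5%. T0-T2: 465 + 508 = 973, or 79%.

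**2. Where the second wave falls.** If T0 is a first wave taken *s* months before diagnosis (0 < *s* < 24), the second wave falls at 24 − *s* months after it, so between 0 and 24 months. It is therefore split between T1 (54%) and T2 (55%). Surveys well beyond that come from another cohort.

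**3. Weight of the late surveys on a linear slope.** Place each survey at its window midpoint (T0 at −1 year) and the open-ended T10 at 9.5 years. Mean time is 1,236/1,231 = 1.004 years. The sum of n(t − mean)² is:

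| Windows | Surveys | Sum of squares | Share |
|---|---|---|---|
| T0-T2 | 973 | 1,995 | 30% |
| T3-T5 | 166 | 940 | 14% |
| T6-T10 | 92 | 3,614 | 55% |
| All | 1,231 | 6,549 | |

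With T10 at 12 years the late share is 60%. This treats surveys as independent. With a random slope (SD 1 point/year, assumed) late surveys are downweighted and carry about 30-45% of the slope information.

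**4. Benign reasons for the fall.** Enrollees are sampled at random, and surveys end in 2016. If diagnoses were spread evenly over the 17 years 1998-2014 (assumption), those from 2011 or earlier can reach 5 years (14/17 = 82%) and those from 2007 or earlier can reach 9 years (10/17 = 59%).

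**5. Direction and size, by simulation.** The documents give no mortality, slope SD or RT split, so every setting here is assumed: 60% RT, 30% high comorbidity, slope SD 1, comorbidity mortality HR 2, two waves for all, then thinned re-sampling at rates modelled on Table 1. Each scenario used five runs of 6,000 women and a random-intercept, random-slope model. True slopes: overall −0.50, RT × time 0, comorbidity × time −0.30.

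| Scenario | Overall | RT × time | Comorbidity × time |
|---|---|---|---|
| Random re-sampling only | −0.49 | 0.00 | −0.27 |
| Death unrelated to own slope, RT HR 0.7 | −0.46 | −0.01 | −0.27 |
| Moderate link to own slope, RT HR 0.7 | −0.38 | −0.04 | −0.23 |
| Strong link, RT HR 0.7 | −0.30 | −0.06 | −0.20 |
| Strong link, RT HR 0.5 | −0.27 | −0.09 | −0.21 |

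The first row shows that differences of about 0.03 are simulation noise. With a link, the overall decline is understated by 0.12-0.23 here. Two further simulations under other assumed settings gave 0.09-0.13 and about 0.04-0.17. One of them put the comorbidity slope 0.025-0.041 too shallow and the RT slope at −0.026 to −0.071.

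**6. RT shift against its precision.** With Table 1 counts, 465 women and assumed variances (slope SD 1, intercept SD 7-8, residual SD 5-7, 60% RT), the standard error of γ11 is about 0.20-0.26. A shift of 0.03-0.09 is 0.03/0.26 = 0.1 to 0.09/0.20 = 0.45 standard errors.

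**The case against.** The strongest reply is that a likelihood-based growth model already handles loss that depends on variables in the model and on observed scores. RT and comorbidity class are both in the model. A reader might infer that the plan's hypotheses about RT, comorbidity and mortality contradict the model, but they do not: bias needs death or drop-out to depend on a woman's unobserved course beyond these, and no passage says that it does. This stands, and the second row of the simulation table supports it.

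A reader might also take the 55% at T2 as the start of attrition. It is not: T1 and T2 together hold 508 surveys for 465 women, and a postdiagnosis survey was required for entry. Nor is the whole later fall survivorship (step 4). T10 is open-ended, so its 4% is not a yearly figure.

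A third tempting reading is that RT-related decline is understated, or that the γ11 rule will wrongly declare RT harmful. Under the plan's own mortality hypothesis the shift would go towards overstating decline with RT, and at this sample size it would rarely decide a test by itself.

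Finally, a condensed article may leave missing-data methods to a fuller plan, and growth mixture models can capture nonlinear patterns. The first would answer a complaint about omission alone. Here the article itself fixes a 10-year claim and a reading of γ11, and lists an informative-loss analysis for one aim only. Nonlinearity does not address who is still surveyed.

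**Conclusion.** The point holds in limited form. The later part of the Aim 1 trajectory rests on 92 surveys from women who survived and were surveyed again, and these have far more influence on a linear slope than their number suggests. Nothing in Aim 1 tests whether that selection matters.

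The bias is conditional. With random re-sampling alone it is essentially nil. If death or drop-out depends on a woman's own HRQOL course, the overall decline is understated by roughly 0.04-0.23 points a year across the settings tried, and the comorbidity slope by a smaller amount. The RT slope moves by about −0.03 to −0.09 if RT also lowers mortality, with shifts clearly beyond simulation noise mainly under the stronger link. That is small against its standard error. The direction follows from the assumed link, and the sizes are illustrative. The point affects what may be concluded about years 5-10 more than the validity of the primary RT test.

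**What to change.** Keep the planned growth model as the primary analysis and add two Aim 1 sensitivity analyses, reported beside it:

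- (a) The same RT and comorbidity contrasts restricted to surveys before 24 months after diagnosis (T0-T2, 973 of 1,231 surveys), where follow-up depends least on re-sampling.
- (b) A joint model of HRQOL and time to death, with RT and comorbidity class in both parts, using the SEER death dates already obtained for Aim 2. With about 2.65 surveys per woman a shared random slope may not be identifiable. Allow in advance for a simpler link, such as a shared random intercept.

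Describe the ≥5-year trajectory as that of surviving, re-surveyed women. Amend the reading of γ11 so that a negative value is not taken as an RT effect on HRQOL without considering selective survival.

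No new data are needed. The cost is extra modelling, wider intervals in the added analyses and a more modest claim beyond 5 years.

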**Functional status**
Difficulty in moderate activitiesDifficulty bathingDifficulty dressingDifficulty eatingDifficulty using the toiletDifficulty walkingDifficulty getting in/out of chairsChest pain with exertionChest pain at restShort of breath at restShort of breath walkingShort of breath with stairs
**Chronic medical conditions**
Angina pectoris/coronary artery diseaseHypertensionMyocardial infarctionCongestive heart failureStrokeEmphysema, asthma, or chronic obstructive pulmonary diseaseDiabetes, high blood sugar, or sugar in urineCrohn disease, ulcerative colitis, or inflammatory bowel diseaseArthritis of hip/kneeHeart attackSciaticaDepression

Based on a literature review, potential confounders included age, race/ethnicity, smoking, body mass index, socioeconomic status (income and education), SEER region, rurality, lag time since treatment, disease stage, tumor grade, and molecular subtype. The year of diagnosis was also included as a covariate in the statistical model to control for variability in diagnostic or treatment criteria over 17 years (1998-2014). Demographics, general information pertaining to treatment status (surgery and radiation), and tumor-related factors (stage, grade, and tumor molecular subtype) were obtained from sources such as the SEER Patient Entitlement and Diagnosis Summary File, the Enrollment Database maintained by the Centers for Medicare & Medicaid Services, and self-reported information.

#### Statistical Analysis Plan

Regarding the descriptive analyses, the baseline characteristics of the study population will be described in terms of the mean and SD for continuous variables and frequencies with percentages for categorical variables. Descriptive analyses will be conducted to compare demographic, tumor-related, and treatment-related factors for the study population by their treatment status (BCS and RT vs BCS only). Differences in continuous variables and categorical variables will be assessed by *t* tests and chi-square tests, respectively. All analyses will be conducted using SAS 9.4 (SAS Institute Inc.) and R 4.0.1 (R Core Team), and a 2-tailed α level of .05 will denote statistical significance.

The probability of the treatment received by a particular person will be estimated by generalized boosted models using receipt of RT as the dependent variable and the baseline characteristics, such as age at diagnosis, race/ethnicity, smoking status, income, education, SEER region, rurality, disease stage, tumor grade, tumor subtype, and year of diagnosis, as the independent variables. Then, the inverse of the probability of receiving the treatment the patient actually received conditional on the observed covariates will be calculated and included as a weight for each patient in subsequent analyses [41]. Balances in potential confounding factors between the treatment groups will be assessed using diagnostic tools, including chi-square tests for categorical variables, *t* tests for continuous variables, and the standardized mean differences between 2 groups [42]. The standardized mean difference will be calculated as the difference in means or proportions divided by a pooled estimate of SD. A standardized mean difference≥10% will be considered as evidence of imbalance [43].

Regarding the estimation of RT and comorbidity effects on HRQOL trajectory, we will use a multilevel growth mixture model with surveys clustered within the women to test whether a difference exists in the patterns of HRQOL trajectories with receipt of RT and comorbidity class after controlling for confounders. At level 1, we will first regress woman i’s HRQOL change, which describes how each woman’s HRQOL depends on time t. This procedure will provide the intercept and slope of the time predictor for each woman. At level 2, we will regress each woman’s intercept and slope on her RT treatment (yes/no) and comorbidity class, adjusted for confounders. This procedure will feature how individual HRQOL change trajectories vary across treatment groups (RT) and comorbidity burden classes (COM). Equation (1) presents a simplified model with no covariates, predicting HRQOL from years after diagnosis (TIME), radiation treatment (RT), and comorbidity class (COM). It will estimate the intercepts and slopes for the group of women.

HRQOL_ti_ = γ_00_ + γ_01_RT_it_ + γ_02_COM_i_ + γ_10_TIME_it_ + γ_11_RT_i_TIME_it_ + γ_12_COM_i_TIME_it_ + error **(1)**

where

γ_00_=Estimated average HRQOL in the year of diagnosis for women who did not receive RT

γ_01_=Value added to the average HRQOL if the women received RT

γ_02_=Value added to the average HRQOL due to the comorbidity class

γ_10_=Change in HRQOL for all women for each year from diagnosis

γ_11_=Additional change for each year if the women received RT

γ_12_=Additional change for each year due to the comorbidity class

A significant negative value on γ_11_ will indicate that women who receive RT experience steeper declines in HRQOL over time than those who did not receive RT, while a significant negative value on γ_12_ will indicate stronger HRQOL declines due to the comorbidity burden.

We will also test for the existence of a differential effect of RT on the HRQOL trajectory according to the comorbidity burden class by incorporating interaction terms in the model. If we lack the power to detect statistically significant differences according to comorbidity level but point estimates for the effect of RT indicate that meaningful differences are present across levels of comorbidity, separate estimates will be reported for each comorbidity class. As each participant completed MHOS at different time points, growth mixture modeling is more flexible and sensitive than traditional repeated-measures analysis [44]. It can also capture nonlinear patterns [44].

Regarding the sensitivity/subgroup analysis, if the sample size allows, subgroup analysis by age and tumor stage will be conducted to examine whether the findings are generalizable to all patients satisfying the eligibility criteria.

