**Objective:**

The proposed study aims to examine the associations of RT with HRQOL trajectories as well as survival outcomes among older women with 5-10 years of follow-up. We will also assess whether prediagnosis comorbidity burden influences receipt of RT and whether the associations between RT and HRQOL trajectory and survival outcomes are modified by the comorbidity burden.

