On the other hand, some older women tend to forego RT (even when necessary) due to cost, inconvenience, and uncertainty of potential adverse responses associated with RT. Limited evidence suggests that older women are more concerned about HRQOL declines rather than fear of recurrence when they make treatment decisions [20,21]. However, understanding HRQOL change with the addition of RT among this population is limited due to the under-representation of older women and those with comorbidities in clinical trials [22,23]. Many studies have evaluated adverse effects on HRQOL with receipt of RT, but most of them were cross-sectional designs or assessments of short-term changes within 1 year post RT [18,24-28]. Not many studies have evaluated the long-term effects of RT on HRQOL. In an older study, Lundstedt and colleagues reported that 10.3% of women had weekly pain even after 10-17 years of RT, and this observation was significantly higher among women who received adjuvant RT than those who did not (1.7%, *P*=.001) [29]. Therefore, we need to update long-term HRQOL with more data since there have been many advancements in RT techniques over the past 3 decades. Moreover, baseline HRQOL is a major predictor of subsequent HRQOL; thus, longitudinal evaluation of HRQOL trajectory in a cohort study design, rather than a cross-sectional evaluation of post-treatment HRQOL, will provide more valid estimates of the impact of RT on HRQOL.

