Few studies have investigated the effect of RT among older women with varying comorbidity burden, and to our knowledge, none of the previous studies have evaluated long-term HRQOL trajectories post RT within older women treated in the modern era. Thus, the proposed study aims to examine the effects of RT on long-term HRQOL trajectories and survival outcomes among older women with low-risk breast cancer in an observational setting. Minimizing the potential bias due to treatment selection and controlling for potential differences in confounding factors between treatment groups are essential in observational comparative effectiveness studies without randomized treatment [30]. To mitigate this concern, first, we will only select older women with low-risk breast cancer whose main treatment plan includes BCS and endocrine therapy with RT being an option. Among this group of women, only 3.3% undergo chemotherapy [1]; thus, the confounding effect of chemotherapy on HRQOL and survival outcomes is minimal. Second, to further balance out the potential confounding factors between the 2 groups, we will use inverse probability of treatment weighting (IPTW) methods, a type of propensity score analysis [31-34], which we have applied successfully in other projects [35,36]. All potential confounding variables will be included in the statistical models when deriving the weights for each group.

This comparative effectiveness study will utilize a national sample of older women to provide much-needed evidence regarding the combined effects of RT and comorbidity on HRQOL (subjective outcome) and survival (objective outcome) in older women. This research has 2 aims.

Regarding Aim 1, we will examine the effect of RT on the HRQOL trajectory over time and its interaction with comorbidity burden in older women with low-risk breast cancer (n=465) using IPTW-adjusted growth mixture models. We hypothesize that the HRQOL trajectory will differ by treatment status and comorbidity burden, and the largest decline will be observed in older women with the highest comorbidity burden.

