60≤*t*<72	T_6_	29 (6)
72≤*t*<84	T_7_	21 (5)
84≤*t*<96	T_8_	17 (4)
96≤*t*<108	T_9_	8 (2)
108≤t	T_10_	17 (4)

We considered comorbidity burden as the effect modifier. Prediagnosis comorbidity is an important component of this study, as it likely impacts HRQOL and survival outcomes adversely while also affecting treatment decisions. The presence and number of comorbidities as well as their severity are important. However, the severity of each comorbidity is not available from MHOS, whereas the functional limitations and symptoms related to these comorbidities are. To account for functional limitations and symptoms as a component of comorbidity, we created a new variable named “comorbidity burden class” with 24 self-reported items (ie, 12 chronic medical conditions, 7 functional difficulties, and 5 symptoms) in MHOS (Textbox 1) using latent class analysis. This technique has been applied successfully to identify healthy patients or comorbidity profiles of cancer patients in studies using SEER-MHOS and the National Cancer Database [39,40] when the severity of comorbid conditions is not available. To identify the prediagnosis comorbidity burden class, the survey completed within 24 months before cancer diagnosis was evaluated. Latent class analysis is a subset of structural equation modeling, which is used to categorize subjects into a set of homogeneous groups (eg, k distinct membership classes of comorbidity) according to the observed variables (eg, self-reported chronic medical conditions, functional status, and symptoms). We anticipated that this procedure would suggest 3-5 distinct categories. We selected the most parsimonious number of classes using the Bayesian information criterion to find the best fitting numbers of classes. The classes of comorbidity burden will be tested as effect modifiers.

Items included in latent class analysis modeling for comorbidity burden class.

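### The printed propensity covariates omit comorbidity burden class, BMI and prediagnosis HRQOL, which leaves the weighted survival curves, the balance check and the RT level term exposed

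*Protocol article*

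**What the plan says.** All places are in the protocol article.

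- **Introduction, on the weights:** "All potential confounding variables will be included in the statistical models when deriving the weights for each group".
- **Introduction, on prediagnosis HRQOL:** "baseline HRQOL is a major predictor of subsequent HRQOL".
- **Abstract, Objective:** the study will assess "whether prediagnosis comorbidity burden influences receipt of RT".
- **Aim 1, Measurements, on comorbidity:** "it likely impacts HRQOL and survival outcomes adversely while also affecting treatment decisions". The role assigned to it there is "We considered comorbidity burden as the effect modifier". Aim 2, Measurements, gives it the same role.
- **Aim 1, Measurements, confounder paragraph after the item box:** "potential confounders included age, race/ethnicity, smoking, body mass index, socioeconomic status (income and education), SEER region, rurality, lag time since treatment", followed by stage, grade and molecular subtype, with year of diagnosis added as a covariate. Comorbidity class and prediagnosis HRQOL do not appear.
- **Aim 1, Statistical Analysis Plan:** generalized boosted models are fitted "using receipt of RT as the dependent variable and the baseline characteristics, such as age at diagnosis", and the list continues as "age at diagnosis, race/ethnicity, smoking status, income, education, SEER region, rurality, disease stage, tumor grade, tumor subtype, and year of diagnosis". Balance is then assessed on the potential confounders, with a standardized mean difference (SMD) of 10% or more read as imbalance.
- **Aim 2:** the confounders match those of Aim 1, the weighting procedure is the same, and the Kaplan-Meier curves incorporate the weights.

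**The concern.** A variable that affects both the choice of RT and the outcome is a confounder, and the article describes comorbidity in those terms. Using it as an effect modifier does not remove the need to balance it. Weights built without it make the arms comparable only on the listed variables.

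Weighting is the article's main protection against treatment selection, and the Aim 2 hypothesis is that RT improves 5-year mortality. If women with heavier comorbidity receive RT less often, the weighted survival curves will favour RT even when it does nothing, and that would look like confirmation. The balance table would give no warning, because it follows a confounder list that does not contain the class.

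**Working it through.** The article gives no figure for this bias, so there is none to reproduce. The check is a comparison of lists, then of models, then an illustration with assumed inputs.

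**1. The lists**

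| Variable | Said to matter | Confounder list (Aim 1, Measurements) | Propensity list (Aim 1, Statistical Analysis Plan) |
|---|---|---|---|
| Comorbidity burden class | Affects treatment decisions and outcomes | No | No |
| BMI | Potential confounder | Yes | No |
| Prediagnosis HRQOL | Predicts later HRQOL | No | No |
| Lag time since treatment | Potential confounder | Yes | No |

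An analyst who combines the Introduction's commitment with the confounder list would add BMI to the weights, but would still leave out comorbidity class and prediagnosis HRQOL.

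**2. Where another adjustment exists**

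- *Aim 1 growth model.* Intercept and slope are regressed on RT and comorbidity class, adjusted for confounders. Confounding by class is addressed in the outcome model.
- *Aim 2 Cox model.* It is described as estimating the effects of both RT and comorbidity. If both are in the model, confounding by class is addressed.
- *Aim 2 Kaplan-Meier curves.* The weights are the only adjustment. The same holds for any weighted estimate with RT alone.
- *γ01 in Equation (1).* The prediagnosis survey (T0) is part of the outcome series, not a covariate. If the arms differ before diagnosis by a constant d points beyond what class and the covariates explain, γ01 takes up d, although RT cannot have caused it. A constant difference leaves the slope term γ11 unchanged.

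**3. Illustration (all inputs assumed; true RT effect null)**

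Let 30% of women be in a high-burden class, with RT use a in the rest and b in that class. Five-year death is 10% in the rest and q in the high-burden class. Other covariates are ignored.

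- Prevalence of high burden: c1 = 0.3b / (0.7a + 0.3b) with RT; c0 = 0.3(1−b) / (0.7(1−a) + 0.3(1−b)) without.
- SMD = (c1 − c0) / √{[c1(1−c1) + c0(1−c0)]/2}.
- Mortality r = 0.10 + (q − 0.10)c in each arm; apparent HR = ln(1−r1) / ln(1−r0).

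Worked case, a = 0.70, b = 0.60, q = 0.20: c1 = 0.18/0.67 = 0.269; c0 = 0.12/0.33 = 0.364; r1 = 0.127; r0 = 0.136; HR = 0.93.

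| RT use, rest vs high burden | c1 vs c0 | Absolute SMD | HR, q = 20% | HR, q = 30% |
|---|---|---|---|---|
| 70% vs 60% | 0.269 vs 0.364 | 0.21 | 0.93 | 0.88 |
| 70% vs 50% | 0.234 vs 0.417 | 0.40 | 0.86 | 0.78 |
| 75% vs 40% | 0.186 vs 0.507 | 0.72 | 0.77 | 0.66 |
| 60% vs 70% (reversed) | 0.333 vs 0.243 | 0.20 | 1.08 | 1.13 |

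Every case exceeds the plan's 0.10 limit. Within class the HR is 1.00 throughout, so a model that conditions on class removes this bias, as would adequate balance on class in the weights.

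**The case against.** **The list is open.** It is introduced by way of examples, the Introduction promises all potential confounders, and the Overview clusters women by comorbidity before obtaining the propensity score. A condensed article may leave the final covariate list to a fuller plan. This stands so far: the article does not prove that comorbidity will be excluded. It does not settle the matter, because the confounder list, which says what the potential confounders are, also leaves the class out, and the class is given a different role.

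**The outcome models already adjust for class.** This stands for the Aim 1 growth model and, as described, for the Aim 2 Cox model. A reader might infer that every weighted estimate in both aims stays confounded; the documents do not support that.

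**Not all three variables are said to drive RT choice.** This also stands. Only comorbidity is tied to both treatment and outcome. No section says that prediagnosis HRQOL affects receipt of RT. The class also contains functional and symptom items that overlap with physical HRQOL. BMI is listed as a potential confounder, so it falls under the stated adjustment in Aim 1 and its balance would be checked.

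**The direction is unknown.** Correct. The Objective poses the influence of comorbidity on RT as a question, and the Measurements section gives no sign.

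**Lag time since treatment.** One might object to it as a post-exposure variable, but it is not in the propensity list, so removing it would not change the printed weight model.

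**Conclusion.** The inconsistency is real and worth correcting before the weights are built. The article describes comorbidity as a confounder and promises to weight on all confounders, yet names the class in neither list; BMI is in one list and not the other.

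The consequences are limited to four places: the weighted Kaplan-Meier curves, any RT-only weighted estimate, the balance check (silent on class and prediagnosis HRQOL), and the RT level term γ01. The slope term γ11, which the plan uses to judge steeper decline, and the Cox estimate conditional on class are largely protected from confounding by class, provided those outcome models are correctly specified.

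The illustrated hazard ratios, 0.66 to 0.93 in one direction and 1.08 to 1.13 in the other, rest wholly on assumed prevalences, RT use and mortality. They show that plausible imbalance could matter; they do not estimate this study's bias.

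**What to change.** - Add comorbidity burden class, BMI, and the prediagnosis physical and mental component scores to the generalized boosted model for both aims, and print the covariate list as closed.
- Include these variables in the overall SMD check under the existing 10% criterion.
- Where class-specific RT effects are estimated, report within-class SMDs descriptively, without a hard limit. With 465 women and, for illustration, four equal classes and equal arms, there are 465/8 ≈ 58 women per arm per class. The chance standard error of an unweighted SMD is then about √(2/58) = 0.19, so a 10% rule would often fail by chance.
- Reconcile the Introduction's commitment, the comorbidity paragraph, the confounder list and the propensity list. State that the class is both a confounder and an effect modifier.

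The cost is small. The class has already been derived, and both aims require a survey within the 24 months before diagnosis. The weights may become slightly more variable.
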